- blood tests for immunogenicity (antibodies against the S protein and RBD of SARS-CoV-2, neutralising antibodies against SARS-CoV-2, cellular immune response assessment [separate cohort^[[5]](#footnote-5)^])
- blood sampling for immune response exploratory analyses
- assessment of the signs and symptoms of acute respiratory infection (in the case of any signs and symptoms related to COVID-19 after immunisation, it is necessary to follow the procedures described in section 8.3)
- assessment of adverse events
- registration of concomitant treatments.

1. Visit 5 (Day 28)

The following procedures will be performed during this visit:

- limited physical examination, including the examination of the injection site
- measurement of body temperature
- recording of vital signs
- blood tests for immunogenicity (antibodies against the S protein and RBD of SARS-CoV-2, neutralising antibodies against SARS-CoV-2, neutralising antibodies against Ad5, cellular immune response assessment [separate cohort^1^])
- analysis for IgM and IgG antibodies to SARS-COV-2
- blood sampling for immune response exploratory analyses
- blood IgE test
- haematology
- biochemistry
- coagulation test
- urinalysis
- assessment of the signs and symptoms of acute respiratory infection (in the case of any signs and symptoms related to COVID-19 after immunisation, it is necessary to follow the procedures described in section 8.3)
- assessment of adverse events
- registration of concomitant treatments.

1. Follow-up period/Phone calls (Month 2, 3, 4, 5)

The study doctor will contact the volunteers during Month 2, 3, 4, and 5 to collect the following:

- information on adverse events
- information on concomitant treatments
- information on the signs and symptoms of acute respiratory infection (in the case of any signs and symptoms related to COVID-19 after immunisation, it is necessary to follow the procedures described in section 8.3).

After that, the information about SAEs and concomitant treatments related to the SAEs will be registered in the subject’s CRF.

1. Follow-up Period/Month 6

The following procedures will be performed during this visit to the trial site:

- limited physical examination, including the examination of the injection site
- measurement of body temperature
- recording of vital signs
- blood tests for immunogenicity (antibodies against the S protein and RBD of SARS-CoV-2, neutralising antibodies against SARS-CoV-2, neutralising antibodies against Ad5, cellular immune response assessment [separate cohort^[[6]](#footnote-6)^])
- blood sampling for immune response exploratory analyses
- blood HIV test
- assessment of the signs and symptoms of acute respiratory infection (in the case of any signs and symptoms related to COVID-19 after immunisation, it is necessary to follow the procedures described in section 8.3)
- registration of SAEs and concomitant treatments regarding the SAEs.

1. Permissible Deviations from the Schedule of Visits and Procedures

Permissible deviations from the schedule of visits (visit windows) are shown in Table 14.

1. Unscheduled Visits and Early Withdrawal Visit
2. Unscheduled Visit

Volunteers may come to an unscheduled visit to receive medical care.

To register an unscheduled visit, the investigator should indicate the date and reason for such visit in the source documents and CRF together with the results of all procedures and examinations performed during such visit. If the reason for the visit is an adverse event/reaction or if an adverse event/reaction is identified during the unscheduled visit, such adverse event will be registered in an established manner.

1. End of Study Visit

Study completion according to the Protocol means the completion of all scheduled visits. Early withdrawal from the study is possible due to reasons specified in sections 5.4.5 and 5.4.6.

In the case of early withdrawal of a randomised and vaccinated volunteer, the investigator should collect as much information as possible about the subject’s condition at the time of the withdrawn. For volunteers withdrawn before the follow-up period, procedures expected at Visit 5 (Day 28) will be performed at the End of Study Visit. For volunteers withdrawn during the follow-up period, procedures expected at Visit 6 (Month 6) will be performed.

The feasibility of blood sampling for immunology tests at the Early Withdrawal Visit should be considered by the investigator and the Sponsor on an individual basis.

The results of examinations performed at the End of Study Visit will be included in the source documents and the CRF together with the reason for the volunteer’s withdrawal.

1. Protocol Deviations

A protocol deviation is any change, divergence, or departure from the study design or procedures described in the clinical trial protocol. The investigator is responsible for reporting protocol deviations upon discovery. The decision to withdraw the volunteer with protocol deviations from the study should be made on an individual basis and agreed with the Sponsor.

Each deviation will be documented on a case-by-case basis and reviewed by the contract research organisation and the Sponsor before the database lock. All protocol deviations will be listed and summarised in the clinical trial report.

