13. Administration of immunotropic drug products (immunomodulatory agents, immunostimulants, immunosuppressants), allergy medications and cytotoxic drugs for > 10 consecutive days within the last 3 months (except for inhaled and topical glucocorticosteroids [GCs]) or the administration of these drugs less than 4 weeks before screening.
14. Administration of immunoglobulins or transfusion less than 3 months before screening.
15. Administration of antipyretics (including nonsteroidal anti-inflammatory drugs and anilides) within 24 hours before randomisation.
16. Blood donation or blood loss (≥450 mL of blood or plasma) less than 3 months before screening.
17. Vaccination within 6 months before screening or unwillingness to skip any other vaccination during the study.
18. History/data of alcohol and drug use/drug abuse or mental disorders.
19. Major surgery scheduled for the next 6 months or performed within the last 6 months before screening.
20. Piercings, permanent makeup/tattoos made less than 1 month before screening or during the study.
21. Pregnancy or lactation.
22. Participation in another clinical trial within 3 months before screening.
23. Psychological, physical or other reasons not allowing the subject to comply with conditions and procedures of the Protocol.
24. Subjects who are employees of healthcare facilities and in contact with persons diagnosed with COVID-19.
25. Subjects who are employees at the trial site.
26. Other reasons not allowing the subject to participate in the study in the opinion of the study doctor.
27. Inclusion of Volunteers Incapable of Giving Informed Consent

It is not intended to include volunteers who are incapable of giving informed consent.

1. Premature Withdrawal from the Study

According to the World Medical Association Declaration of Helsinki and other applicable regulatory documents, a volunteer may withdraw from the study at any time and due to any reason.

Study subjects may be prematurely withdrawn from the study in the case of early termination of the study upon the Sponsor’s decision (section 5.4.6).

Additionally, study subjects may be prematurely withdrawn from the study due to the following reasons:

1. Subject’s request to discontinue for any reason.
2. Development of conditions not meeting the subject’s eligibility criteria for the study (the decision to exclude the subject should be made by the investigator and agreed with the Sponsor on an individual basis).

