When signing the Informed Consent Form, all women of childbearing potential and men whose partners are women of childbearing potential should agree to use proper contraception methods during the study from the moment of signing of the Informed Consent Form and until the end of the follow-up period.

Requirements for registration and reporting of pregnancy cases are provided in section 8.4.2.8.9.

The following subjects are considered women of non-childbearing potential:

- postmenopausal women, i.e. women who had no menstruations for 12 consecutive months without any alternative medical reason
- women who underwent sterilisation (for example, bilateral tubal ligation more than one menstrual period before the enrolment, hysterectomy or bilateral oophorectomy).

Proper (reliable) contraception methods include:

1. Complete abstinence [periodic abstinence (for example, rhythm or symptothermal methods) is not a proper contraception method].
2. Male sterilisation (with the corresponding post-vasectomy confirmation of the absence of sperm in the ejaculate).
3. Intrauterine device or intrauterine system.
4. Hormonal methods of contraception: oral, injectable or implantable hormonal contraceptives. Women who use hormonal methods of contraception should use the specific method for at least 6 months before the administration of the study drug and should continue to use such method during the entire study until the end of the follow-up period.
5. Condom in combination with a spermicide (foam/gel/cream/film/suppositories).
6. Occlusive cap (diaphragm, cervical or vault caps) with a spermicide (foam/gel/cream/film/suppositories).
7. Double-barrier method: condom and occlusive cap (diaphragm, cervical or vault caps) with a spermicide (foam/gel/cream/film/suppositories).

Other Restrictions

On days of blood sampling for laboratory assessments, volunteers should come to the visit fasted.

During the first 14 days after vaccination, the volunteers should observe the following precautions against novel coronavirus infection as strictly as possible:

- Avoid travelling to other regions, using public transport and visiting crowded places (except for visits to the trial site).
- Avoid close contacts with persons with acute respiratory infection symptoms.
- Keep a 1.5-meter distance from others in public places, use disposable medical masks and change them every 2 hours.

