1. STUDY METHODOLOGY
   1. Schedule of Visits and Procedures

The study design includes 7 outpatient visits to trial sites and 5 phone calls with the study doctor:

- Visit 0 (screening) — Day −10...Day −1
- Visit 1 (randomisation, vaccination), phone contact in 5–8 hours — Day 0
- Visit 2 — Day 2
- Visit 3 — Day 7
- Visit 4 — Day 14
- Visit 5 — Day 28
- Follow-up period/Phone calls (Month 2, 3, 4, 5)
- Follow-up period/Visit 6 — Month 6

The total duration of the subject’s participation in the study will be about 6.5 months (about 205 days). The study flowchart is shown in Figure 9 (section 5.1).

The schedule of visits and procedures is presented in Table 14 below.

The investigation of the cellular immune response will be performed in a separate cohort of at least 60 subjects randomised at trial sites in Moscow.

Table 14 Schedule of Visits and Procedures

| **Study visit** | **Visit 0 (V0)** | **Visit 1 (V1)** | **Visit 2 (V2)** | **Visit 3 (V3)** | **Visit 4 (V4)** | **Visit 5 (V5)** | **Phone contact** | **Visit 6 (V6)** |
| --- | --- | --- | --- | --- | --- | --- | --- | --- |
| **Study day/month** | **Day −10–−1 (screening)** | **Day 0^1^ (vaccination)** | **Day 2 [V1 + 2 days]** | **Day 7 [V1 + 7 days]** | **Day 14 [V1 + 14 days]** | **Day 28 [V1 + 28 days]** | **Month 2 (V5 + 1 month)**  **Month 3 (V5 + 2 months)**  **Month 4 (V5 + 3 months)**  **Month 5 (V5 + 4 months)** | **Month 6 (V5 + 5 months)** |
| **Visit window** | **-** | **-** | **+ 1 day**^2^ | **± 1 day** | **± 1 day** | **± 1 day** | **± 5 days** | **± 15 days** |
| Informed consent | • |  |  |  |  |  |  |  |
| Demographics/medical history^3^ | • |  |  |  |  |  |  |  |
| Prior treatments | • | • |  |  |  |  |  |  |
| Analysis for IgM and IgG antibodies to SARS-COV-2^4^ | • |  |  |  |  | • |  |  |
| Analysis of SARS-COV-2 RNA (PCR) | • | *If COVID-19 is suspected, a nose and throat swab will be taken at home twice with the interval of 3 days* | | | | | | |
| Height, body weight, BMI | • |  |  |  |  |  |  |  |
| Physical examination, including neurologic examination^5^ | • | • | • | • | • | • |  | • |

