^1^Within 2 hours after vaccination, the volunteers must be observed at the trial site for systemic and local reactions to the vaccine administration, including immediate hypersensitivity. In 20 minutes (± 5 minutes) and 2 hours (± 10 minutes) after the vaccine administration, the examination of the injection site, body temperature and vital signs measurement, and AEs and concomitant treatment registration will be performed. In 2 hours (± 10 minutes), an additional limited physical examination will be performed. In 5–8 hours after vaccination, the study doctor will contact the volunteer by phone to collect data on AEs and concomitant treatment.

^2^Visit 2 is performed in 48–72 hours after vaccination.

^3^During the collection of medical history at screening, it is necessary to ask the volunteer about the signs and symptoms of COVID-19 (section 8.3) and obtain epidemiological anamnesis (regarding close contacts with persons suspected for SARS-CoV-2 infection or persons with laboratory-confirmed COVID-19 within the last 14 days).

^4^Tests for IgM and IgG antibodies to the N protein and IgG antibodies to the S protein of SARS-CoV-2 at screening and tests for IgM and IgG antibodies to the N protein of SARS-CoV-2 at Visit 5 (Day 28).

^5^Comprehensive physical examination is performed only at screening. At other visits, a limited examination is performed (general appearance, ears, nose, throat, skin and injection site, lymph nodes, cardiovascular system, respiratory system, and neurological system).

| **Study visit** | **Visit 0 (V0)** | **Visit 1 (V1)** | **Visit 2 (V2)** | **Visit 3 (V3)** | **Visit 4 (V4)** | **Visit 5 (V5)** | **Phone contact** | **Visit 6 (V6)** |
| --- | --- | --- | --- | --- | --- | --- | --- | --- |
| **Study day/month** | **Day −10–−1 (screening)** | **Day 0^1^ (vaccination)** | **Day 2 [V1 + 2 days]** | **Day 7 [V1 + 7 days]** | **Day 14 [V1 + 14 days]** | **Day 28 [V1 + 28 days]** | **Month 2 (V5 + 1 month)**  **Month 3 (V5 + 2 months)**  **Month 4 (V5 + 3 months)**  **Month 5 (V5 + 4 months)** | **Month 6 (V5 + 5 months)** |
| Vital signs ^6^ | • | • | • | • | • | • |  | • |
| Body temperature^7^ | • | • | • | • | • | • |  | • |
| Electrocardiography | •^8^ |  | • |  |  |  |  |  |
| Infections^9^ | • |  |  |  |  |  |  | • |
| Haematology^10^, biochemistry^11^, coagulation test^12^, urinalysis^13^ | • |  | • |  |  | • |  |  |
| Blood IgE test | • |  |  |  |  | • |  |  |
| Urine pregnancy test^14^ | • |  |  |  |  |  |  |  |

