| Evaluation of inclusion/exclusion criteria | • | • |  |  |  |  |  |  |
| Randomisation |  | • |  |  |  |  |  |  |
| Vaccination |  | • |  |  |  |  |  |  |

^6^Arterial pressure, heart rate, breathing rate.

^7^Additionally, the volunteers should measure the body temperature at home by themselves within 7 days after vaccination (in 5–8 hours after the vaccine administration on the day of immunisation and then twice daily (morning and evening) until Visit 3 (Day 7)). During trial site visits, the volunteers should tell the study doctor about all increases in body temperature.

^8^ECG results obtained not more than 30 days before screening are also acceptable.

^9^Human immunodeficiency virus (HIV), syphilis, HBV and HCV. At Visit 6, only HIV test is performed.

^10^Haematology: haemoglobin, haematocrit, RBC, platelets, WBC, WBC differential and ESR.

^11^Biochemistry: total protein, ALT, AST, ALP, LDH, total bilirubin, creatinine, urea, fasting glucose, C-reactive protein.

^12^Coagulation test: aPTT, PT, fibrinogen.

^13^Urinalysis: specific gravity, pH, protein, glucose, erythrocytes, leucocytes, casts.

^14^For women of childbearing potential.

| **Study visit** | **Visit 0 (V0)** | **Visit 1 (V1)** | **Visit 2 (V2)** | **Visit 3 (V3)** | **Visit 4 (V4)** | **Visit 5 (V5)** | **Phone contact** | **Visit 6 (V6)** |
| --- | --- | --- | --- | --- | --- | --- | --- | --- |
| **Study day/month** | **Day −10–−1 (screening)** | **Day 0^1^ (vaccination)** | **Day 2 [V1 + 2 days]** | **Day 7 [V1 + 7 days]** | **Day 14 [V1 + 14 days]** | **Day 28 [V1 + 28 days]** | **Month 2 (V5 + 1 month)**  **Month 3 (V5 + 2 months)**  **Month 4 (V5 + 3 months)**  **Month 5 (V5 + 4 months)** | **Month 6 (V5 + 5 months)** |
| Reactogenicity evaluation^15^ |  | • | • | • |  |  |  |  |
| Blood tests for the S protein and RBD of SARS-CoV-2, neutralising antibodies against SARS-CoV-2, cellular immune response assessments^16^ |  | • |  |  | • | • |  | • |
| Blood test for neutralising antibodies against Ad5 |  | • |  |  |  | • |  | • |
| Blood sampling for immune response exploratory analyses |  | • |  |  | • | • |  | • |
| Assessment of the signs of acute respiratory infection^17^ |  |  | • | • | • | • | • | • |
| Registration of concomitant treatment^18^ |  | • | • | • | • | • | • | • |
| Registration of adverse events^19^ |  | • | • | • | • | • | • | • |

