- obtaining written informed consent for participation in the study
- collection of demographic data (date of birth, sex, race, substance abuse)
- collection of medical history (prior and concomitant diseases) including prior or current signs and symptoms of COVID-19 (section 8.3) and epidemiological anamnesis (regarding close contacts with persons suspected for SARS-CoV-2 infection or persons with laboratory-confirmed COVID-19 within the last 14 days)
- assessment of prior treatments (including previous vaccinations)
- measurement of height, weight and body mass index (BMI)
- comprehensive physical examination
- measurement of body temperature (axillary temperature)
- recording of vital signs
- analysis for SARS-COV-2 RNA (PCR)
- analysis for IgM and IgG antibodies to SARS-COV-2
- analysis for infections (HIV, syphilis, HBV, HCV)
- haematology
- biochemistry
- coagulation test
- urinalysis
- urine pregnancy test (for women of childbearing potential)
- blood IgE test
- ECG (results obtained not more than 30 days before screening are also acceptable)
- evaluation of inclusion/exclusion criteria.

At the end of the screening period, the study doctor should evaluate the examination results to confirm the subject’s eligibility.

1. Vaccination/Visit 1 (Day 0)

Successfully screened and eligible subjects will come to the trial site for vaccination.

The following procedures will be performed during the visit:

- assessment of prior treatments
- limited physical examination, including the examination of the injection site
- measurement of body temperature
- recording of vital signs
- evaluation of inclusion/exclusion criteria
- randomisation
- blood tests for immunogenicity (antibodies against the S protein and RBD of SARS-CoV-2, neutralising antibodies against SARS-CoV-2, neutralising antibodies against Ad5, cellular immune response assessment [separate cohort^[[4]](#footnote-4)^]), blood sampling for immune response exploratory analyses
- vaccination.

Within 2 hours after vaccination, the volunteers must be observed at the trial site for systemic and local reactions to the vaccine administration, including immediate hypersensitivity.

In 20 minutes (± 5 minutes) after the vaccine administration, the following procedures will be performed:

- examination of the injection site
- measurement of body temperature
- recording of vital signs
- assessment of systemic and local reactions to the vaccine administration (section 8.4.2.1)

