1. STUDY PROCEDURES AND ENDPOINTS
   1. Collection of Demographic and Other Baseline Characteristics
      1. Demographics

The following demographic data will be registered at screening:

- date of birth
- sex
- race
- substance abuse: smoking, drinking, drug use, drug abuse.
  - 1. Medical History

During screening, detailed medical history data will be collected, including the information about all current and significant (according to the investigator) prior diseases.

Information about all prior and current diseases at screening or diseases that occur during the interval from the signing of the informed consent form until the administration of the investigational product will be noted in the Medical History section of the subject’s Case Report Form (CRF). CRFs should at least include the following information: diagnosis/symptom, onset date and end date (if resolved).

Any untoward medical occurrence in a volunteer administered the investigational product should be registered as an adverse event.

During the collection of medical history at screening, it is necessary to ask the volunteer about the signs and symptoms of COVID-19 (section 8.3) and obtain epidemiological anamnesis (regarding close contacts with persons suspected for SARS-CoV-2 infection or persons with laboratory-confirmed COVID-19 within the last 14 days).

- - 1. Prior/Concomitant Treatment

CRFs should include information about the treatment of prior and current diseases, including medications and non-medication treatment. In this study, prior therapy will be registered within 3 months before randomisation, and the information about vaccinations will be collected within 6 months before screening.

The subject’s CRF should also include data on any concomitant treatment performed after the enrolment and until Visit 5 (Day 28). After that, concomitant treatments regarding SAEs should be registered.

- - 1. Height, Body Weight, BMI

Height, body weight and body mass index (BMI) will be measured at screening.

- - 1. Urine Pregnancy Test

A urine pregnancy test will be performed for women of childbearing potential.

The test will be done at the central laboratory using urine test strips. The investigators will be provided with a separate laboratory manual containing detailed instructions on handling biological samples (collection, storage and transportation).

- - 1. Blood Analysis for Infections

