- In addition to submission of expedited reports, the Sponsor will be preparing annual reports on vaccine safety throughout the whole study, including all new information obtained during the reported period. Such reports will be submitted to regulatory authorities at least once a year or with other intervals at the request of such authorities.

1. Pregnancy

The pregnancy itself is not an adverse event, except when there are grounds to believe that the administration of the investigational product has led to reduced efficacy of contraceptives. Any congenital anomalies and malformations in children of the volunteers are serious adverse events. Scheduled abortions carried out by medical indications, as well as any serious complications during the pregnancy (including spontaneous abortions), will be recorded as serious adverse events. Scheduled abortions without complications are not adverse events.

All pregnancies recorded during the study (including pregnancies of sex partners of the volunteers taking part in the study) will be properly registered.

In the case of confirmed pregnancy, the investigator should notify the contract research organisation/Sponsor about it within not more than 24 hours after obtaining the information by sending a completed pregnancy report form. Then, the information on the pregnancy outcome should be submitted. Pregnancy will be registered from the time of the vaccine administration until the last procedure conducted during the study.

The outcome of each pregnancy case (spontaneous abortion, elective abortion, birth of a normal child or a child with congenital anomalies or malformations) must be also registered.

During the collection of medical history at screening, pregnancies occurred within 30 days before vaccine administration should be registered and evaluated.

- - 1. Acceptability of Endpoints

Methods of efficacy evaluation selected for this trial are widely used during clinical and epidemiology studies of vaccines. As far as there are no special criteria to evaluate vaccine efficacy against novel coronavirus infection COVID-19, the criteria used in the previous studies of Ad5- nCoV have been chosen. The safety assessment methods used in this trial are generally accepted for clinical trials of vaccines.

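### Pregnancy is an exclusion that is re-evaluated at Visit 1, but no pregnancy test or history update is scheduled there, and the screening history cannot cover the 30 days asked of it

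*Protocol*

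**What the plan says.** - **Criterion.** Exclusion 21 in Protocol section 5.4.3 reads "Pregnancy or lactation".
- **When eligibility is judged.** The Table 14 row "Evaluation of inclusion/exclusion criteria" is marked at Visit 0 and at Visit 1. Section 6.2.2 lists the second evaluation before randomisation and vaccination.
- **When pregnancy is tested.** The Table 14 row "Urine pregnancy test^14" has one mark, at Visit 0. The text agrees: section 6.2.1 lists "urine pregnancy test (for women of childbearing potential") among the screening procedures, and neither section 6.2.2 nor any later visit list contains it.
- **How it is tested.** Section 8.1.5 names no visit, and says "The test will be done at the central laboratory using urine test strips".
- **Screening window.** Section 6.1 gives "Visit 0 (screening) — Day −10...Day −1". Section 6.2.1 allows procedures to be spread over several days or done on Day −1.
- **Contraception.** Section 5.5 sets the general duty "from the moment of signing of the Informed Consent Form and until the end of the follow-up period". Hormonal users must also have used their method for at least 6 months before the study drug. No lead-in is stated for the other accepted methods.
- **Pregnancy history.** Section 8.4.2.8.9 says: "During the collection of medical history at screening, pregnancies occurred within 30 days before vaccine administration should be registered and evaluated". In Table 14, medical history is marked at Visit 0 only.

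**The concern.** An eligibility check repeated just before dosing is useful for a criterion only if something current stands behind it. For exclusions 2 and 3 it does, because temperature and blood pressure are measured again at Visit 1. For exclusion 21 the schedule provides neither a new test nor an updated history. A woman whose pregnancy was too early to show at screening can therefore be randomised and given a single, irreversible dose with every listed procedure followed, and no deviation would be recorded.

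Separately, section 8.4.2.8.9 gives sites an instruction that they cannot carry out as written, because a history taken at screening cannot describe the days between screening and vaccination. What is at stake is participant safety and correct application of an eligibility criterion, not the statistical inference.

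**Working it through.** The protocol states no figure on this point, so there is none to reproduce. The check has three steps.

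**1. Age of the test and history at vaccination.** Vaccination is on Day 0 and screening runs from Day −10 to Day −1.
- Longest gap: 0 − (−10) = 10 days.
- Shortest gap: 0 − (−1) = 1 day.
- Pregnancy tests scheduled at Visit 1: none.

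**2. Coverage of the 30-day history window.** A history taken on Day −g can cover at most 30 − g of the 30 days before vaccination.
- Day −10: 30 − 10 = 20 days, so up to a third of the window (10/30) is missed.
- Day −1: 30 − 1 = 29 days.

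The window is not fully covered on any permitted screening day, although the shortfall is only one day at best.

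**3. What a second strip at Visit 1 could add.** Suppose a strip becomes positive some fixed time L after conception. The protocol does not give L. A strip on Day −g finds conceptions up to Day −g − L; a strip on Day 0 finds those up to Day −L. The difference is a span of g days, whatever L is. With n women of childbearing potential and an annual conception rate r:

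extra conceptions found = n × r × g / 365

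The gap g (1 to 10 days) comes from section 6.1. The protocol gives neither n nor r; I assume n = 100 to 200 of the 500 randomised and r = 2 to 10 % per year.

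| n | r | g (days) | n × r × g / 365 |
|---|---|---|---|
| 100 | 2 % | 1 | 0.005 |
| 150 | 5 % | 1 | 0.02 |
| 150 | 5 % | 10 | 0.21 |
| 200 | 10 % | 10 | 0.55 |

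Each row gives every woman the same gap, so the last row supposes that all were screened on Day −10. The formula also applies r to all n women. Hormonal users with 6 months of prior use should conceive less often, and if L is shorter than g, part of the span falls after consent, when contraception is required. For a given n and r, both points make the result an overestimate.

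**The case against.** **The test timing is consistent, so this is a design preference.** True as far as the test goes: Table 14 and section 6.2.1 agree, and section 8.1.5 does not conflict. The only textual mismatch is between the history instruction in section 8.4.2.8.9 and the timing of screening.

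**Visit 1 is not empty.** The criteria are evaluated again, section 7.1 requires an examination for contraindications before immunisation, and section 8.1.2 has diseases arising between consent and dosing recorded in the medical history. A pregnancy that is known or suspected can therefore be acted on. This stands, but section 7.1 names only temperature as its example, pregnancy is not a disease, and none of these provisions schedules a test or a question about pregnancy.

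**Stronger readings that the documents do not support.**
- A reader might infer that no woman needs contraception before consent. Section 5.5 rules that out for hormonal users; the gap concerns women using methods without a lead-in.
- A reader might infer that recent conceptions necessarily reach vaccination undetected. The documents show only that they can: the gap may be one day, and an investigator may learn of a pregnancy at Visit 1.
- A reader might count every conception in, say, the two weeks before screening, which on the same assumptions gives 0.08 (100 × 2 % × 14/365) to 0.77 (200 × 10 % × 14/365). The two-week detection limit is not in the protocol, and a Visit 1 strip gains only the 1 to 10 day gap.
- A reader might see a threat to the analysis, because pregnancy is a reason for withdrawal and randomised subjects are not replaced. Withdrawal is discretionary under section 5.4.5, and at most about half a subject among 500 randomised is negligible when section 9.1 puts the requirement at 180 analysed.

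**A second strip does not close the blind window.** It moves the window forward by 1 to 10 days, and very recent conceptions are still missed. This stands and limits the claim.

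**Conclusion.** The point holds as a minor safety and eligibility improvement. Exclusion 21 is re-evaluated at Visit 1 with no scheduled test or history update behind it, the available information being 1 to 10 days old. The 30-day history in section 8.4.2.8.9 cannot be obtained at screening: at most 20 of the 30 days are covered from Day −10 and 29 from Day −1. Both statements rest on the protocol alone.

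The expected yield of a second strip, about 0.005 to 0.55 conceptions in the trial, rests on assumed numbers of women and conception rates that the protocol does not supply. It should be read as an order of magnitude: below one case. The primary analysis, the sample size and the error rate are unaffected.

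**What to change.** 1. In Table 14 and section 6.2.2, add an update of the pregnancy history at Visit 1, before randomisation. Reword section 8.4.2.8.9 so that the 30-day history is completed at that visit, which reconciles it with the schedule.
2. In Table 14 and section 6.2.2, repeat the urine strip at Visit 1 for women of childbearing potential, before randomisation.
3. Amend section 8.1.5 so that the Visit 1 strip may be read at the site. The section now sends the strip to the central laboratory and states no turnaround time, so it does not ensure a result before randomisation at the same visit.

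The cost is one strip per woman of childbearing potential and one history question at a visit that already takes place, plus on-site reading and its documentation. The text changes are two marks in Table 14 and short edits to three sections. The history update alone makes section 8.4.2.8.9 workable and costs almost nothing; the strip adds the small gain shown above.
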